#### Intervention fidelity checks

Fidelity to treatment protocols in both arms will be ensured by: a) having therapists submit a completed checklist following each session; b) regular review of submitted session checklists; c) therapist participation in monthly group supervision; and d) recording of therapy sessions. A random selection of 10% of recordings will be assessed by the research team using a modified version of the revised cognitive therapy scale (CTS-R; [44]). The scale was designed to assess therapist competency in cognitive therapy, and has good psychometric properties [44]. The scale assesses skills specific to cognitive therapy, general therapeutic skills including therapeutic alliance and has been modified to include competency in skills necessary for the FCR intervention that are not otherwise covered by the CTS-R. Feedback will be given where non-fidelity is identified, as recommended by the validated ‘Method of Assessing Treatment Delivery’ [45].

#### Pilot study

A pilot study of the intervention was carried out between October 2010 and December 2011 [22]. Results are presented in detail elsewhere [22]. In brief, ten psychologists / psychiatrists took part in a 1-day training session held in October 2010. In post-training questionnaires, all therapists had increased knowledge about and confidence in managing FCR. At the close of the pilot 4 therapists had recruited 8 participants (2 each). Recruitment was 83% and retention rates 100%. Both patients and therapists were highly satisfied with the intervention. Patients reported finding the intervention very helpful and had a significant and clinically meaningful reduction in FCR as measured by the FCRI.

### Outcomes

All participant outcomes are assessed using either an online or paper and pencil self-report questionnaire containing the measures listed below. Participants are posted or e-mailed, as preferred, the questionnaires, to be completed and returned in a reply-paid envelope or online. Questionnaires are completed upon enrollment in the study prior to randomisation, immediately after treatment completion, 3 and 6 months after treatment completion. The researchers follow up participants who do not return their questionnaire within two weeks, with up to three phone calls at different times of the day according to a pro forma. If phone contact cannot be made, email and text reminders are sent where possible. Finally, a replacement questionnaire is sent 3 weeks after the non-returned questionnaire.

#### Primary outcome

Fear of Cancer Recurrence is assessed using the 42-item FCRI [39], the most comprehensive multi-dimensional scale of FCR available, and suitable for patients with mixed cancer diagnoses. It has been found to be internally consistent (Chronbach’s α=0.75 to 0.91 across subscales) and stable over a two-week interval (ρ = 0.58 to 0.83 across subscales), and has a robust factor structure. The FCRI has convergent validity with other standardised measures of FCR (ρ = 0.66 to 0.77) and discriminant validity with QOL amongst a large sample (n = 600) of Canadian cancer patients with mixed tumours [39]. Respondents rate the degree to which symptoms or issues affect them on a Likert scale ranging from 0 (‘not at all’ or ‘never’) to 4 (‘a great deal’ or ‘all the time’). Higher scores indicate higher FCR.

#### Secondary outcomes

•Cancer-specific distress is assessed with the 22 item Impact of Event Scale [46] with two subscales: intrusion and avoidance.

•General distress is assessed with the Depression, Anxiety, Stress Scale, 21 item short form [47,48].

•Quality of life is assessed with the AQoL8D, a 35 item health-related QOL instrument that includes domains of mental health, coping, self-worth, happiness, relationships, along with the other subscales assessing functional aspects of QOL; independent living, pain, and senses. The AQoL8D [49,50] also allows the calculation of quality-adjusted-life years (QALYs) through the health state utility scoring algorithm.

•Unmet needs are assessed using the 8 item Information sub-scale of the Survivors Unmet Needs Survey, which includes needs relating to finding information, knowing which information to trust and worrying about cancer recurrence and spread [51].

•Treatment satisfaction is evaluated using a single question assessing overall satisfaction with the therapy.

#### Exploratory outcomes

•Metacognitions (the cognitive processes, strategies, and knowledge that are involved in the regulation and appraisal of thinking itself.’[52]) are measured with the Metacognitions Questionnaire-30 [52,53], a 30 item questionnaire with 5 subscales measuring: cognitive confidence; positive beliefs about worry; cognitive self-consciousness; uncontrollability and danger; and need to control thoughts.

•Fear of cancer recurrence will also be measured using the Concerns About Recurrence Questionnaire (CAR-Q), a 5 item purpose designed questionnaire developed by BT and PB, to act as a brief screen of FCR. This is to test the psychometric properties of the CAR-Q.

#### Potential covariates

Clinical and demographic information will include age, time since diagnosis, marital status, education, parity, stage of disease, treatment received (both medical and psychological) and current treatment (e.g. anti-depressants (if any)). In addition individual level of perceived risk of cancer recurrence will be assessed as this may influence firstly level of FCR prior to treatment and also treatment efficacy. Other potential covariates related to treatment are therapeutic alliance and treatment expectancy and credibility. Therapeutic alliance, which has consistently been shown to be associated with treatment outcome [54], will be assessed using the 12-item Working Alliance Inventory short-form revised (WAI-SR) [55]. The WAI-SR assesses the agreement on goal, the agreement on tasks that achieve the goal, and bond between patient and therapist. Treatment expectancy, which has been shown to predict treatment outcomes in a variety of contexts [56], will be measured using the 6-item Credibility/Expectancy Questionnaire [57].

#### Therapist measures

Training evaluation is completed by participating therapists immediately after training completion. The evaluation survey includes items surveying: basic demographic features, professional qualifications and experience, confidence in dealing with FCR pre- and post-training, and satisfaction with the intervention training content and delivery using purpose designed Likert scales. This survey was used in our previous pilot study [22].

#### Economic measures and analysis

Economic evaluation will be a cost-consequences analysis conducted from both the broad societal perspective and the narrower perspective of the health care sector. The economic evaluation will compare any incremental costs of the intervention (costs accrued in the intervention arm compared to costs accrued in the control arm) to the full list of incremental outcomes (including QALYs in a cost-utility analysis). The intervention costs in the evaluation will include only the costs of intervention delivery, (excluding development or research costs), to estimate the resource use required if the intervention was rolled-out into practice across Australia. The research team and provider records will be used to determine the costs of the intervention (screening costs, cost of intervention delivery and intervention materials).

Other costs associated with each arm of the trial will be estimated using a resource use diary. The diary will be used to document and measure health behaviours and service use - such as hospitalisation, other allied health consultations, use of alternative therapies and self-monitoring behaviours. The diary will also document days out-of-role (including paid and unpaid work) travel costs and carer costs. The diary will be based on existing resource use questionnaires used in national databases and will cover both costs paid for by the individual as well as those paid for by third parties (such as an insurance company). Measured resource use will be valued using existing unit costs from sources such as the Australian Refined Diagnosis Related Groups (AR-DRG). AR-DRG for costs of hospitalisation and Australian Bureau of Statistics estimates of Australian earnings for productivity effects. Based on previous research, questionnaires have been found to be reliable estimates of resource use [58].

Uncertainty in the cost and outcome data will be further evaluated through nonparametric bootstrap analysis. The sensitivity of economic evaluation results to the methods of evaluation will be tested through sensitivity analyses, whereby key evaluation parameters (such as unit costs), are varied to assess the impact on the study conclusions.

#### Sample size

This is a longitudinal randomised controlled trial, with one baseline measure and 3 post-intervention measures. The primary outcome is the Fear of Cancer Recurrence Inventory, a 42 item scale with a possible range of 168.

We based our sample size calculation on 90% power, a two-sided α = 0.05 t-test, dropout of 30%, a difference between groups of 14.5, and a standard deviation of 29 [39] (a standardised effect size of 0.5). The sample size calculations should account for the clustering of outcomes by therapist, and although there is no published intra-cluster correlation (ICC) for the FCRI, we took guidance from two large reviews on ICCs in similar contexts [59,60] and used an ICC of 0.01. Assuming a total of 20 therapists, and following Donner and Klar, [60,61] the required sample size is 13 patients per therapist, for a total of 260 patients. If dropout is lower, for example, 20% then this sample size allows for a larger intra-cluster correlation or a small detectable difference. This sample size also gives 90% power to detect a difference of 0.5SD between the groups in each of the secondary outcomes. The value includes attrition of 30%, however, we expect attrition to be lower, since patients with FCR report a high level of need for help, and we experienced low attrition when piloting the intervention.

#### Statistical analysis

Analyses will be by intention-to-treat. Linear mixed models will be used to account for the hierarchical, non-independent nature of the data: repeated measures on patients nested within therapist. A saturated time x treatment model with unstructured covariance structure will be used to guard against misspecification of the model. Random effects of patient and therapist will be used. The primary analysis will be the comparison at the each of the 3 post-baseline (post-treatment) time points of the two arms using a contrast within this mixed model. Overall pattern of change will be assessed by testing the treatment by time interaction. Adjusted analysis, including using baseline FCRI, sex, age, time since diagnosis, cancer type, perceived risk, treatment expectancy and therapeutic alliance will also be investigated. Variables will be included in the model if they have a Kendall’s Tau correlation higher than 0.1 with FCRI. Mixed models yield unbiased estimates for data which are missing completely at random and at random [62], however, if the amount of missing data for the primary outcome is greater than 20%, sensitivity analyses will be performed by multiply imputing the missing data, and adding and subtracting clinically plausible amounts from the imputed values. These new datasets will be re-analysed, to see how conclusions change.

Secondary outcomes (QoL, distress, unmet information needs) will be analysed in a similar way to the primary outcome. Treatment satisfaction and therapist training evaluation will be described with descriptive statistics. To see if colorectal and breast cancer patients responded differently to the treatment, we will test the interaction cancer type x treatment x time. Predictors of FCR, distress and QoL at baseline will be explored using multiple linear regression. The relationship between Metacognition and FCR will examined using 1) regression to see if there is a relationship at baseline in the entire sample and then 2) using mediation techniques following the methods of Baron and Kenny [63] in the treatment group only, immediately post baseline (time 1). The CAR-Q will be compared with the FCRI using psychometric techniques.

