### Aims

The aims of this study are to evaluate in a randomised controlled trial (RCT), the efficacy and cost efficacy of a therapist-delivered intervention (Conquer Fear) in reducing the impact of FCR in disease-free breast and colorectal cancer survivors with clinical levels of FCR, compared to a relaxation training control intervention. Secondary aims are to evaluate patient satisfaction with the program and the relative cost-effectiveness of Conquer Fear and the relaxation interventions. Specific hypotheses are that:

1. Participants in the Conquer Fear intervention will have lower scores on the Fear of Cancer Recurrence Inventory of at least 14.5 (0.5 standard deviation) as compared to the attention control group (who receive relaxation therapy) at follow-up;

2. Participants in Conquer Fear will have less cancer specific distress, less anxiety and depression, better quality of life, fewer unmet needs, and less maladaptive metacognitions when compared to the control group;

3. Patients receiving Conquer Fear will find the therapy program useful for treating their FCR and be satisfied with the program; and

4. The Conquer Fear intervention will be cost-effective compared to the relaxation comparator intervention.

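### Three visit-specific comparisons are all called the primary analysis, but the trial is sized for one 0.05 test and no success rule is stated

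*Protocol article*

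**What the plan says.** Three parts of the protocol article bear on this.

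- **Statistical analysis.** "The primary analysis will be the comparison at the each of the 3 post-baseline (post-treatment) time points of the two arms", to be done "using a contrast within this mixed model". The section then adds a separate item: "Overall pattern of change will be assessed by testing the treatment by time interaction".
- **Outcomes.** Post-baseline questionnaires are completed "immediately after treatment completion, 3 and 6 months after treatment completion", which gives the three visits.
- **Sample size.** "We based our sample size calculation on 90% power, a two-sided α = 0.05 t-test, dropout of 30%, a difference between groups of 14.5", with SD 29, ICC 0.01 and 20 therapists, leading to 260 patients. This is a calculation for one comparison.

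Hypothesis 1 in Aims does not settle the visit. It expects a difference "as compared to the attention control group (who receive relaxation therapy) at follow-up". The Primary outcome section names the instrument (the 42-item FCRI) but no visit. The article gives no order of testing, no gatekeeper and no rule for combining the three comparisons.

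**The concern.** The article defines three primary comparisons and plans error and power for one. The trial's conclusion therefore depends on a rule that is not written down. A difference at the end of treatment that has gone by 6 months could be reported as a positive primary result under one reading and as a failed trial under another.

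This matters more than usual here. The Previous interventions section faults earlier programmes because their effects were immediate but not sustained, or because no long-term data were published. Which visit carries the claim is thus close to the scientific question itself, and it cannot be settled credibly once the results by visit are known.

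**Working it through.** **Step 1. Reproduce the plan's figure.** Inputs from Sample size: difference 14.5, SD 29, two-sided 0.05, power 90%, dropout 30%, ICC 0.01, 20 therapists with 13 patients each.

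- Per arm, before inflation: 2 × [29 × (1.960 + 1.282) / 14.5]² = 84.06, so 168.1 in total.
- Completers per therapist: 13 × 0.7 = 9.1. Design effect: 1 + (9.1 − 1) × 0.01 = 1.081.
- Total: 168.1 × 1.081 / 0.7 = 259.6, which matches 260.
- Power at 260 (91 completers per arm, design effect 1.081): 90.0%.

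So 260 is right for one comparison at one visit.

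**Step 2. Error if any one visit counts.** The quantity is P(max |Z| > 1.96) for three correlated standard normal statistics under no effect. The article gives no between-visit correlation for the FCRI total. The nearest figure is the two-week stability of the subscales, 0.58 to 0.83 (Primary outcome), which I use only as a guide. Equal correlations are assumed.

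| Correlation | Any visit, either direction | Any visit, favouring Conquer Fear | All three visits, either direction |
|---|---|---|---|
| 0.4 | 13.1% | 6.6% | 0.2% |
| 0.5 | 12.5% | 6.3% | 0.3% |
| 0.58 | 12.0% | 6.0% | 0.5% |
| 0.7 | 10.9% | 5.5% | 0.9% |
| 0.8 | 9.8% | 5.0% | 1.4% |
| 0.83 | 9.4% | 4.7% | 1.6% |

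The references are 5% for the second column and 2.5% for the third. Independent tests would give 1 − 0.95³ = 14.3%. A correlation of 0.9 gives 8.4%. A correlation that decays with distance between visits (first-order autoregressive) gives 12.9% at 0.5 and 8.8% at 0.9, so the pattern matters little.

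**Step 3. Power under the other rules.** The expected test statistic at the planned difference is 14.5 / (29 × √(4 × 1.081 / 182)) = 3.24.

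- All three visits required, planned effect at each: about 77% (correlation 0.4) to 83% (0.8 to 0.83).
- Bonferroni, 0.05 / 3 = 0.0167 per visit, critical value 2.394: power per visit Φ(3.244 − 2.394) = 80%. To restore 90% per visit needs about 334 patients.

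**Step 4. A side check on hypothesis 1.** It expects scores "lower scores on the Fear of Cancer Recurrence Inventory of at least 14.5 (0.5 standard deviation) as compared to the attention control group". The smallest observed difference that reaches p < 0.05 with 182 completers and the design effect is 1.96 × 29 × √(4 × 1.081 / 182) = 8.8 points, well short of 14.5.

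**The case against.** **The error rate is conditional.** A reader might infer that the trial's false-positive rate simply is 10 to 13%. The article does not support that. The figure needs the any-visit rule, which is stated nowhere; under an all-visits rule the error is below 2%. It also needs an assumed correlation, and it counts both directions. This objection stands: the error rate is undefined rather than known to be inflated.

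**Nothing licenses picking the best visit.** Also true. The text commits the team to all three contrasts. But it does not say how three results become one conclusion.

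**Multiplicity belongs in the SAP.** This is a journal article and the SAP is not shown, so the lack of an adjustment procedure is not in itself a finding. What remains is what the article does state: three comparisons share primary status while the sample size covers one. A SAP that picked one visit would be changing that definition, not filling a gap.

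**The overall test may protect the contrasts.** The treatment-by-time test is given its own purpose, the pattern of change, and no contrast is made conditional on it. The singular word for contrast could be read as one joint test, but the sentence places the comparison at each visit. If one joint or averaged contrast was meant, the text still has to say so.

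**The Bonferroni loss depends on the effect.** The 80% is per visit. With the planned effect at all three visits, the chance that at least one passes Bonferroni is about 95% at correlation 0.5 and 90% at 0.8. The loss bites when the effect is confined to one visit.

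**The 14.5 points are a separate matter.** Sizing on a relevant difference and testing against zero is standard practice. Only the wording of hypothesis 1 is loose, and error control is not affected.

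**Conclusion.** The point holds in conditional form. The article gives primary status to three comparisons, sizes the trial on "a two-sided α = 0.05 t-test", and states no success rule, so 5% error and 90% power do not both describe the primary conclusion.

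- Any visit suffices: two-sided error about 9 to 13% for correlations from 0.83 down to 0.4 (8.4% at 0.9). A false positive favouring Conquer Fear is about 4.7 to 6.6% against 2.5%.
- All visits required: error below 2%, power about 77 to 83%.
- Bonferroni: power about 80% per visit.

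The ambiguity is certain from the text. The percentages rest on an assumed correlation, and the power figures also assume the planned effect at the visits concerned. It would be wrong to conclude that 260 is miscalculated; it reproduces for the single comparison it was built on. Because this governs the trial's headline claim, it should be settled before unblinding.

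**What to change.** Before unblinding, name one post-treatment visit as the single primary comparison, in both hypothesis 1 (Aims) and Statistical analysis. The emphasis on lasting benefit in the Background bears on which visit is chosen; the choice is the team's.

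Make the other two visits key secondary. One way is to test them in a prespecified order at 0.05, each only if the one before is significant. This holds the familywise error at 5% and keeps 260 patients and 90% power for the primary test. A single averaged contrast over the three visits, Holm's procedure, or an explicit all-visits rule would also remove the ambiguity. The power of whichever is chosen would then have to be stated.

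The cost is wording in the protocol, any SAP and the registration; no patients or data are added. The downside is that the other visits cannot carry the claim if the primary one fails.

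As a minor, separate edit, word hypothesis 1 as superiority, keep 14.5 as the planning difference, and read the confidence interval against it.

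### The primary between-arm contrast makes no use of baseline FCRI, so it is less precise than the collected data allow; it remains unbiased and keeps its stated power.

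*Protocol article*

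**What the plan says.** The Statistical analysis section of the protocol article specifies the primary model: "A saturated time x treatment model with unstructured covariance structure will be used to guard against misspecification of the model". Random effects for patient and therapist are added. The primary analysis is a contrast between the two arms at each of the three post-treatment times. No covariate and no constraint on the baseline means is named.

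Baseline FCRI comes in only afterwards: "Adjusted analysis, including using baseline FCRI", together with sex, age, time since diagnosis, cancer type, perceived risk, treatment expectancy and therapeutic alliance, is to be investigated as well. Covariates enter that model if their Kendall's tau with FCRI exceeds 0.1.

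The Sample size section describes the design: "This is a longitudinal randomised controlled trial, with one baseline measure and 3 post-intervention measures". It sizes the trial on an unadjusted comparison: "We based our sample size calculation on 90% power, a two-sided α = 0.05 t-test, dropout of 30%, a difference between groups of 14.5", with "a standard deviation of 29 [39] (a standardised effect size of 0.5"). No baseline-to-follow-up correlation is used. The Outcomes section has the first questionnaire completed at enrolment, before randomisation.

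**The concern.** Baseline FCRI is measured before allocation on the same scale as the outcome, so it is a legitimate covariate and a natural one. A saturated model in which each arm has its own free mean at each time does not adjust for it. If baseline is left out of the response vector, the model contains no baseline information at all. If baseline is a level of time, its mean is still free in each arm, so with complete data the follow-up contrast is the raw difference in means. In both cases, variation in follow-up scores that baseline could explain stays in the error of the primary estimate.

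The secondary adjusted analysis is not a clean replacement. Therapeutic alliance, as described under Potential covariates, concerns the patient–therapist bond and agreement on goals and tasks. It can only arise once therapy has begun, and the arm may affect it. The timing of treatment expectancy is not stated. The plan therefore names no analysis that adjusts for pre-randomisation covariates alone.

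What is at stake is the width of the primary confidence interval, and power that could be had without further data.

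**Working it through.** **Inputs from the Sample size section.** Difference 14.5, SD 29, two-sided alpha 0.05, power 90%, 30% dropout, 20 therapists with 13 patients each, and the plan "used an ICC of 0.01". Allocation of 1:1 is assumed; the blocks of 2 and 4 under Randomisation fit this.

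**Step 1: reproduce the stated 260.**
- Per arm: 2 × [29 × (1.960 + 1.282) / 14.5]² = 84.06, so 168.1 in total.
- Evaluable patients per therapist: 13 × 0.7 = 9.1. Design effect: 1 + (9.1 − 1) × 0.01 = 1.081.
- 168.1 × 1.081 / 0.7 = 259.6, matching 260.

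The trial is therefore sized for an unadjusted comparison. At 260 patients the effective total is 260 × 0.7 / 1.081 = 168.4, the SE is 29 × √(4/168.4) = 4.47, and power is 90.0%.

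**Step 2: variance factors, relative to the unadjusted observed difference.** Let r be the baseline-to-follow-up correlation of the total score.
- Adjusted for baseline: 1 − r².
- Saturated model, baseline outside the response vector: 1.
- Saturated model, baseline inside, 30% dropout at random: 1 − 0.3r². The baseline scores of those who drop out recover a little information.
- Power = Φ(0.5 / √(4 × factor / 168.4) − 1.96).

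The article does not give r. Its only figure is a subscale retest: "stable over a two-week interval (ρ = 0.58 to 0.83 across subscales"). Follow-up here runs over months, in patients selected at 13 or more on the severity subscale, so a lower value is plausible. The range 0.3 to 0.6 is an assumption.

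| r | Adjusted factor | Adjusted SE | Adjusted power | Planned power, baseline outside | Variance cut | Planned power, baseline inside | Variance cut |
|---|---|---|---|---|---|---|---|
| 0.3 | 0.91 | 4.26 | 92.5% | 90.0% | 9% | 90.8% | 6% |
| 0.4 | 0.84 | 4.10 | 94.3% | 90.0% | 16% | 91.4% | 12% |
| 0.5 | 0.75 | 3.87 | 96.3% | 90.0% | 25% | 92.1% | 19% |
| 0.6 | 0.64 | 3.58 | 98.2% | 90.0% | 36% | 93.0% | 28% |

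The last column is 1 − (1 − r²)/(1 − 0.3r²); at r = 0.5 this is 1 − 0.75/0.925 = 0.19. A simulation at r = 0.6 without therapist clustering agreed: the adjusted-to-planned variance ratio was 0.64 with complete data, and 0.72 with 30% random dropout and baseline in the response vector.

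**Step 3: a change-from-baseline contrast.** With complete data its variance factor is 2(1 − r), against (1 − r)(1 + r) for adjustment. The change score is less precise for every r below 1: 1.4 against 0.91 at r = 0.3, and 0.8 against 0.64 at r = 0.6.

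**The case against.** The strongest reply is that nothing here is invalid. Sizing and primary analysis agree with each other, an unadjusted primary with an adjusted supporting analysis is a defensible and conservative choice, and the 30% dropout allowance is one the authors expect not to need. That stands. It makes this a point about efficiency.

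The second reply is that the article does not say whether baseline is a level of time and does not give the contrast coefficients, which an analysis plan could settle. That also stands, and it is why the size is shown under both layouts. It does not remove the point: neither layout, nor a change-from-baseline contrast, matches the precision of adjustment.

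Some stronger readings are tempting but not supported:
- A reader might infer that the tau rule could shut baseline FCRI out. Under bivariate normality tau = (2/π) arcsin r, which is 0.19 to 0.41 for r of 0.3 to 0.6. That is well above 0.1, so the rule hardly matters for this variable.
- A reader might infer that the adjusted model uses baseline as both response and covariate. This follows only if baseline is one of the repeated outcomes, which the article does not state.
- A reader might count chance baseline imbalance as a further harm. Its SE is 29 × √(4/260) = 3.6 points, and at r = 0.5 an imbalance of that size shifts the contrast by 1.8 points. That variability is already inside the SE of 4.47, so it is the same loss and not an extra one.
- Nothing in the documents shows that baseline FCRI is the strongest predictor of outcome.

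**Conclusion.** The point holds as a loss of precision in the primary estimate. It is not bias, and it is not a shortfall in power: a reader who inferred an underpowered or invalid trial would be wrong, because the 260 reproduces and gives 90% for the unadjusted follow-up difference.

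For an assumed r of 0.3 to 0.6, the avoidable part of the variance is about 9% to 36% with baseline outside the response vector, and about 6% to 28% with it inside. Power would reach about 92.5% to 98%, from 90% or from about 91% to 93% respectively. These figures rest on the plan's SD, ICC and 30% dropout, on dropout unrelated to outcome, on the same design effect applying to both analyses, and on the assumed r. At the low end the gain is small. The direction does not depend on the value of r, as long as it is not zero.

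**What to change.** Make one of these the primary model:
- a constrained longitudinal model, with baseline and the three follow-up scores as responses and a common baseline mean for both arms; or
- a model of the three post-baseline scores only, with baseline FCRI and baseline FCRI by time as prespecified covariates.

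Include baseline FCRI always, whatever the Kendall's tau rule gives. State whether baseline is a level of time, and write out the contrast. Keep the unadjusted contrast as a supportive analysis. Report any model containing therapeutic alliance separately as exploratory, so that it does not stand in for the baseline-adjusted result.

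The cost is a change of wording in the analysis plan, best made before unblinding. It needs no new data, patients or visits, and the sample size can stay at 260.
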